#### Participant assessment

Table 2 shows the assessment timeline. The data collection will be based on instruments with good psychometric properties, previously used in clinical trials for anxiety disorders to ensure comparability, and with validated French versions (when available).

**Table 2 Tab2:** Study schedule of patient assessment

TIMEPOINT	Web-based screening	Web-based interview and questionnaires-Enrolment	Intervention				
			Follow-up				
	T_**−1**_	T_**0**_		T_**1**_	T_**2**_	T_**3**_	T_**4**_
**INITIAL SOCIODEMOGRAPHIC AND CLINICAL ASSESSMENT**							
Sociodemographic variables	X	X					
Social Phobia Inventory	X						
Panic Disorder Severity Scale	X						
Mini International Neuropsychiatric Interview (MINI)		X					
Disease Burden Morbidity Assessment		X					
Service utilization and medication (past 12 months)		X					
**SYMPTOM-FOCUSED OUTCOMES**							
Generalised Anxiety Disorder – 7	X			X	X	X	X
Beck Anxiety Inventory		X		X	X	X	X
Patient Health Questionnaire – 9	X			X		X	X
**RECOVERY-FOCUSED OUTCOMES**							
Recovery Assessment Scale - Revised		X		X		X	X
Mental Health Self-Management Questionnaire		X		X		X	X
**ECONOMIC EVALUATION OUTCOMES**							
AQoL-6D		X		X	X	X	X
Service utilization and medication (past 4-months)		X		X	X	X	X
**PROCESS MEASURES**							
Working Alliance Inventory			X				
Gross Cohesion Scale			X				
Logbook			X				
**EXPERIENCE WITH THE INTERVENTION**							
Brief qualitative interview						X	X

##### Baseline

Sociodemographic variables will be collected at baseline (T_−1_ et T_0_), and comprise sex and gender, age, marital status, racial identity, ethnicity, education level, income level, occupation, and insurance coverage. We will also collect data on previous experience with mental health services. The web-based screening survey will comprise the Generalised Anxiety Disorder-7 (GAD-7) [45], a 7-item self-report questionnaire measuring anxiety symptomatology. Diagnostic-specific measures will also be administered. The Social Phobia Inventory (SPIN) [46, 47] is a 17-item self-report questionnaire measuring the fear, avoidance, and physiological discomfort associated with social anxiety disorder. Studies have reported good internal reliability, test-retest reliability, and convergent validity [46]. The Panic Disorder Severity Scale Self Report (PDSS-SR) [48] is a questionnaire measuring the severity of seven dimensions of panic disorder. The PDSS-SR shows good internal reliability, test-retest reliability and sensitivity to change [48]. The clinical assessment will be based on the Mini International Neuropsychiatric Interview (MINI) [41], a brief structured diagnostic interview for DSM-5 administered by a trained lay interviewer. Inter-rater reliability will be assessed for 25% of audio-recorded interviews.

##### Primary outcome measure

The severity of anxiety symptoms will be assessed using the self-report, 21-item Beck Anxiety Inventory (BAI) [49, 50]. The BAI assesses emotional, physiological, and cognitive symptoms of anxiety and indicates minimal (0–7), mild (8–15), moderate (16–25) and severe anxiety (26–63). The scale shows significant reliable improvement and clinically significant change cut-points [49–51].

##### Secondary outcome measures

Participants will also complete diagnostic-specific measures, as well as other questionnaires related to quality of life, self-management, and recovery. The Patient Health Questionnaire (PHQ-9) [52] is a 9-item, self -report questionnaire measuring the frequency of depressive symptoms with good reliability and validity. The Assessment of Quality of Life – 6D (AQol-6D) [53] is a valid and reliable 20-item questionnaire assessing six psychosocial and physical dimensions related to the quality of life. The Disease Burden Morbidity Assessment [54, 55] is a self-report questionnaire measuring the presence of chronic conditions and interference on daily activities. The self-administered Recovery Assessment Scale – revised (RAS-r) [56–59] is a 24-item validated patient-oriented outcome measure of recovery in five domains: personal confidence and hope, willingness to ask for help, goal and success orientation, reliance on others, no domination by symptoms. The RAS is the most frequently used and tested recovery measure, has good psychometric properties, including sensitivity to change, and correlates with a range of other measures (e.g., activation, psychological well-being, positive illness outlook). The Mental Health Self-Management Questionnaire (MHSQ) [23] assesses the use of mental health self-management strategies. It comprises 18 items. The scale has satisfactory internal reliability and construct validity, adequate test–retest reliability and its convergent and concurrent validity are supported.

##### Service utilization

Data will be obtained from provincial administrative databases (i.e., *Régie de l’assurance-maladie du Québec* (RAMQ), Quebec emergency department database (BDCU) and public primary health care database (I-CLSC)) for medical and biopsychosocial services, hospitalization’s registry, and medication data at the end of the data collection. A brief questionnaire on other mental health consultations (e.g., type of professional, duration, costs) and psychotropic medication will be administered at each assessment period to offset the limitations of administrative data.

##### Questionnaires completed during SMS sessions

The appreciation of the alliance for both participants and facilitators will be assessed with the 12-item version of the Working Alliance Inventory (WAI) [60, 61]. The WAI shows good construct validity and high internal consistency [62]. The perceived cohesiveness and bond for participants will be examined with the 9-item Gross Cohesion Scale (GCS) [63], a scale with acceptable reliability and validity. These measures will be used at sessions 3 and 8.

A logbook will also be used by facilitators to record intervention adherence for each participant as well as to report experiences and perceptions related to SMS group facilitation. The logbook content will provide a better understanding of the actual implementation of the program. The facilitators will also complete a brief questionnaire comprising sociodemographic questions, items on academic and professional backgrounds, as well as experience with SMS, group interventions and anxiety disorders.

### Embedded qualitative interview

A sequential embedded qualitative approach [64] will be used to explore participants’ views and experiences regarding the SMS intervention. The data collection will include a brief individual telephone contact with open-ended questions at the T_3_ and T_4_ follow-ups. A semi-structured interview guide [65] with open-ended questions will be used to elicit information on topics such as participants’ experience with the intervention, its perceived effectiveness, and most useful strategies or skills acquired. We will obtain verbatim transcripts of all the audio recordings. Data coding and analysis will be conducted based on the interactive cyclical process of data reduction, data display and conclusion drawing and verification [66]. For data reduction, we will use the QSR*NVIVO database software [67] to analyze the transcriptions with a coding strategy based on emerging clustering during the process.

### Data collection, management, and analysis

#### Participant timeline

The assessments will be conducted at baseline (T_−1_, T_0_), posttreatment (T_1_; 4-month post-randomization) and follow up at 8-month (T_2_), 12-month (T_3_) and 24-month (T_4_) post-randomization. In-treatment assessments for participants and facilitators will also be conducted at sessions 3 and 8. Self-report questionnaires at each assessment period will be completed online through the REDCap application managed at the *Centre de recherche du Centre Hospitalier Universitaire de Sherbrooke* (CRCHUS) at University of Sherbrooke on a secure server with systematic backups. The clinical interviews (T_0_, T_3_, T_4_ only) will be conducted with the Zoom video conferencing service. Data collection with the REDCap application will be managed independently of the treatment assignment. The database will only include coded, depersonalised data, and participant’s identifying information will be stored in a separate secure location with restricted access to the linking code.

We conservatively planned for a 25% attrition at follow up, but we will devote considerable efforts toward a < 5% target with study retention strategies: (1) limiting burden and inconvenience (minimal data collection; web-based; secondary direct data capture through administrative databases); (2) minimal dataset for participants identified at high-risk of attrition (BAI, AQoL-6D); (3) monitoring data collection in real time; (4) education strategies on patient engagement and appreciation (e.g. reminders, website), (5) contact of dropouts; (6) information gathering for relocation; (7) financial compensation (20 $ for each follow up assessment); (8) treatment incentives with delayed-access to SMS for control arm to increase perceived health benefits. Follow up measures at 12- and 24-month are more susceptible to attrition (secondary analysis), and we will include a brief web-based interview that will foster patient engagement. Moreover, we will obtain a complete dataset from provincial administrative data on service utilization.

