### Objectives

The aim of the present study is to evaluate the effectiveness of a structured group virtual SMS program as an add-on to treatment-as-usual (TAU) in a sample of adults with anxiety disorders. Primary questions: When group SMS is added to TAU in community-based care for patients with anxiety disorders, is the SMS + TAU group more effective in reducing anxiety symptoms than TAU alone? Secondary questions: a) Considering a recovery-oriented approach for patients with anxiety disorders, is there a significant difference between group SMS + TAU and usual care in terms of self-management strategies and personal recovery assessment at the 12-month follow-up? b) Does group SMS + TAU present superior cost-effectiveness and cost-utility, in terms of quality of life and anxiety-free days, than TAU for patients with anxiety disorders at the 12-months follow-up? c) Is there a significant difference between group SMS + TAU and usual care for high-end functioning rates? d) Is there maintenance of gains at 12- and 24-months follow-up? e) Is there differential effectiveness based on moderators (i.e., sociodemographic characteristics, clinical characteristics, past treatment experience) and mediators (i.e., group cohesion, therapeutic alliance, adherence)?

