#### Recruitment

Recruitment strategies will include self-referral following advertisements (e.g., waiting rooms of clinics, bulletin boards, geo-located website, and social media) and referrals from community-based primary care (e.g., family physician, community organization, mental health care team, mental health provider). The recruitment of participants will be conducted through a two-stage process. *Filter 1:* Self-referred individuals will acquire information on the study by accessing the study’s website or through a telephone call or email to our research laboratory. Self-referred individuals will complete a web-based screening survey comprising the required online consent form, basic eligibility criteria as well as anxiety symptoms and comorbidity overview. The initial web-based consent form and procedure has been approved by the ethics committee. At the end of the survey, they will provide their name and contact information. In the presence of clear exclusion criteria, a list of mental health resources will be provided. *Filter 2:* In the second stage (within 2 weeks of the screening survey), the baseline assessment will be conducted on a secure web-based platform with a trained clinical evaluator. The interview will begin with the consent form. The evaluator will explain the study, review the consent form with the participants, answer their questions, and verbally ask for their consent. The consent form will be sent by email for the participants to read prior to the online assessment, and this verbal consent procedure has been approved by the ethics committee given the web-based data collection method. The assessment will comprise sociodemographic data, service utilization and MINI International Neuropsychiatric Interview [41] for DSM-5 assessment (T_0_; random pre-assignment), combined with an adapted baseline Relief interview procedure (e.g., current main difficulties, interest in the program, capacity to use eLearning technology, readiness to take part in a group intervention). Patients meeting eligibility criteria at T_0_ will be given instructions to complete the remaining web-based self-reported questionnaires within 48 h, and only then will we have all required information to proceed with randomization. Figure 1 shows the study flowchart.

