#### Assignment of interventions: Sequence generation, allocation concealment mechanism and implementation

Participants will be randomized based on stratification for study site, with random block sizes (2, 4, 6) to ensure a balance in the allocation for the strata. The randomization schema will be carried out using a code generated by the study statistician. Concealment will be maintained for the participants, research team, and staff. The REDCap computerized platform will only release the randomization code to the research coordinator based on the allocation sequence after verification of eligibility. The research coordinator will then enrol and assign participants to interventions.

The randomization sequence will be recorded with random codes (“A” and “B”) until the primary outcome analyses are concluded. Masking of trial participants and facilitators is not possible in this trial. Clinical evaluations at T_3_ and T_4_ will not be masked as we will address through qualitative interviews patient experience following the SMS intervention, or readiness to enroll intervention at T_3_ for the control group.

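### The short questionnaire set for patients at high risk of attrition omits both instruments of secondary question (a), so those outcomes go uncollected in a selected group

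*Protocol article*

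**What the plan says.** The Objectives section sets secondary question (a) as a comparison of the arms "in terms of self-management strategies and personal recovery assessment at the 12-month follow-up". Under recovery-focused outcomes, Table 2 schedules the "Recovery Assessment Scale - Revised" (RAS-r) and the "Mental Health Self-Management Questionnaire" (MHSQ) at T0, T1, T3 and T4 for all participants and marks no exception.

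The Participant timeline section then lists eight retention strategies. The second is a "minimal dataset for participants identified at high-risk of attrition (BAI, AQoL-6D"). The same section says "We conservatively planned for a 25% attrition at follow up", sets a target below 5%, and adds: "Follow up measures at 12- and 24-month are more susceptible to attrition (secondary analysis"). It also states that REDCap data collection is run independently of treatment assignment.

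On masking, the assignment section says: "Masking of trial participants and facilitators is not possible in this trial". The Clinical outcomes section plans maximum-likelihood mixed models on all available data, without imputation, and a sensitivity analysis for missing data.

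**The concern.** The trigger for the short set is an identified risk of dropping out. On its face this can include patients who would have completed the MHSQ and RAS-r had they been asked. Risk of attrition is plausibly related to engagement, which is close to what the MHSQ measures, so the unasked patients are unlikely to be a random subset.

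Two things would be at stake. The first is precision on question (a), because these losses add to ordinary dropout at the time point where the article itself expects more of it. The second is possible bias. Likelihood-based analysis of incomplete data is valid when missingness is explained by data in the model, and the risk judgement is not among the covariates that the article names. The rule also removes the self-reported service-use questionnaire, which the Service utilization section includes to make up for gaps in the administrative data.

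**Working it through.** **1. What the short set keeps and drops** (Table 2 against retention strategy 2)

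| Instrument | Follow-up visits in Table 2 | In short set? |
|---|---|---|
| BAI (primary) | T1, T2, T3, T4 | yes |
| AQoL-6D | T1, T2, T3, T4 | yes |
| MHSQ, RAS-r (question a) | T1, T3, T4 | no |
| PHQ-9 | T1, T3, T4 | no |
| GAD-7 | T1, T2, T3, T4 | no |
| Self-reported service use | T1, T2, T3, T4 | no |

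The loss is confined to follow-up. The Recruitment section requires the baseline questionnaires first: "only then will we have all required information to proceed with randomization".

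**2. The plan's own sample size.** Inputs from the Sample size section: difference 4, SD 12.5, so d = 4/12.5 = 0.32; α = 0.05, taken as two-sided; power 80%. The t-test calculation gives 154.3, hence 155 per group. Allowing for 25% attrition, 155/0.75 = 206.7, hence 207 per arm. Both stated figures reproduce. They concern the BAI at T1 and are unaffected by this point.

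**3. Precision for question (a), illustration only.** The article does not give the share f of randomised patients who stay in the trial on the short set, so f is varied here. Patients per arm with MHSQ and RAS-r at T3 number 207 × (1 − attrition − f). Power is Φ(d√(n/2) − 1.96), borrowing d = 0.32 from the BAI and ignoring clustering.

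| f | n per arm, 25% attrition | Power | n per arm, 5% attrition | Power |
|---|---|---|---|---|
| 0 | 155 | 80% | 197 | 89% |
| 5% | 145 | 78% | 186 | 87% |
| 10% | 135 | 75% | 176 | 85% |
| 20% | 114 | 68% | 155 | 80% |

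At 25% attrition, f = 10% leaves 35% of patients without these outcomes and f = 20% leaves 45%. The table assumes that every flagged patient would otherwise have answered, so it is an upper limit on the loss due to the rule.

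**4. Possible shift in the arm difference, illustration only.** If a share f is not asked and scores g SD worse than the rest, the full mean is μ − f·g while the observed mean is μ. The arm difference therefore shifts by g × (f in SMS − f in TAU).

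- Equal shares, same g and same treatment effect: shift 0.
- 20% in SMS, 10% in TAU, g = 0.3 to 0.5: 0.03 to 0.05 SD in favour of SMS.
- 10% in SMS, 20% in TAU, same g: 0.03 to 0.05 SD against SMS.

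The sign depends wholly on which arm has more flagged patients, and the article does not say. These are also shifts in raw means. The planned model can use baseline and earlier MHSQ and RAS-r scores, so any part of g that those scores predict is absorbed.

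**5. Equal shares but unequal benefit.** If flagged patients are 20% of each arm and gain nothing, an observed d of 0.32 corresponds to 0.32 × 0.80 = 0.26 in the full population. The 20% and the zero gain are again assumptions.

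**The case against.** The short set is a deliberate and sensible trade. It keeps the primary outcome and the utility measure in patients who might otherwise give nothing, and some of the lost MHSQ and RAS-r answers would have been lost anyway. This stands, and the fix preserves it.

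A reader might infer that staff flag patients before they have missed or refused anything, using signs such as missed sessions that exist only in the SMS arm. The article does not say who flags, when, or on what signs. The neighbouring strategies (real-time monitoring, reminders, contact of dropouts) fit equally well with flagging after late or missing questionnaires. A condensed article may leave the criterion to the full protocol, so its absence is not itself the point.

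A reader might also infer that the comparison is biased in favour of SMS. The documents do not support that. Data collection is stated to be independent of assignment, and nothing links the facilitators' logbook to the choice of questionnaire set. The one arm-specific retention measure, delayed access to SMS, is aimed at the control arm, so retention concern may lie there. Equal flagging with equal effects gives no bias in the arm difference.

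For the economic question, the BAI and AQoL-6D remain and administrative data still cover part of service use. A missing-data sensitivity analysis is planned. It can gauge the consequences of the loss but cannot recover answers that were never requested.

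**Conclusion.** The point holds as one of avoidable, selective missingness on secondary outcomes. The omission of the MHSQ and RAS-r follows directly from comparing the short set with Table 2 and question (a), and needs no assumption. That the missingness is related to outcome is plausible rather than documented. Bias is possible but unproven, and neither its direction nor its size can be derived from the article. Every share and SD gap used above is an assumption. The precision loss is equally undetermined because the number flagged is not given. The primary analysis is protected, and baseline and earlier scores reduce the risk for question (a). This is a low-cost improvement to secondary outcomes and does not threaten the trial's main conclusion.

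**What to change.** Use one rule in both arms, applied without reference to allocation or session attendance. Present the questionnaires in a fixed order: BAI and AQoL-6D first, then MHSQ and RAS-r, then the rest, with each instrument saved on completion. A patient who stops early then still yields the present minimal dataset. Fall back to BAI and AQoL-6D alone only after the patient has declined or not responded. If the team prefers to keep flagging, require only those two instruments from flagged patients and leave the MHSQ and RAS-r open as an optional continuation. In either case, report by arm how many patients received the short set at each visit.

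The cost is a change of protocol wording and of questionnaire order in REDCap. The downside is a slightly longer request (MHSQ 18 items, RAS-r 24 items) to some patients at risk of dropping out. The optional-continuation variant keeps that burden lowest.

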#### Assignment of interventions: Sequence generation, allocation concealment mechanism and implementation

Participants will be randomized based on stratification for study site, with random block sizes (2, 4, 6) to ensure a balance in the allocation for the strata. The randomization schema will be carried out using a code generated by the study statistician. Concealment will be maintained for the participants, research team, and staff. The REDCap computerized platform will only release the randomization code to the research coordinator based on the allocation sequence after verification of eligibility. The research coordinator will then enrol and assign participants to interventions.

The randomization sequence will be recorded with random codes (“A” and “B”) until the primary outcome analyses are concluded. Masking of trial participants and facilitators is not possible in this trial. Clinical evaluations at T_3_ and T_4_ will not be masked as we will address through qualitative interviews patient experience following the SMS intervention, or readiness to enroll intervention at T_3_ for the control group.

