### Trial design

The trial is a two-arm parallel group multicentre pragmatic superiority randomized controlled trial (RCT), with a 1:1 allocation at the individual level. The group SMS intervention will be offered to participants in the TAU groups after the 12-month follow-up (delayed-intervention). The 24-month follow-up will therefore only provide a within-group dataset. The proposed protocol conforms to SPIRIT guidance [40].

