## Methods

### Participants, interventions, and outcomes

#### Study setting

The study will be conducted in four health administrative regions in Quebec (Canada): Eastern townships, Mauricie-et-Centre-du-Québec, Abitibi-Témiscamingue and Laurentides. Administrative regions were purposefully selected based on the following criteria: a) the in-person group SMS intervention is not currently largely implemented in the region; b) the virtual SMS intervention is rarely accessed by participants from the region, even though the virtual SMS format is technically accessible throughout the province; c) diversity (e.g., population size, region, university teaching hospital).

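### Small published blocks (2, 4, 6) within site, in an unmasked trial, leave the next assignment partly predictable; larger undisclosed blocks are a cheap improvement

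*Protocol article*

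**What the plan says.** The Trial design section sets a two-arm comparison "with a 1:1 allocation at the individual level". Under Study setting, "The study will be conducted in four health administrative regions in Quebec (Canada"); I read these regions as the strata. The assignment section reads: "Participants will be randomized based on stratification for study site, with random block sizes (2, 4, 6) to ensure a balance in the allocation for" each stratum.

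The same section has the study statistician generate the code and claims concealment from participants, research team and staff. REDCap releases each code to the research coordinator only once eligibility has been verified. It continues: "The research coordinator will then enrol and assign participants to interventions". It also says: "Masking of trial participants and facilitators is not possible in this trial". The arms carry letter codes until the primary analyses are finished.

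The Recruitment section gives the baseline interview to a trained clinical evaluator. The interview includes an adapted programme intake procedure, whose examples are "current main difficulties, interest in the program, capacity to use eLearning technology, readiness to take part in a group intervention". Eligible patients then have 48 hours to complete the online questionnaires, and randomization follows only after that.

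**The concern.** Concealment has two parts: nobody can look up the next code, and nobody can work it out. Release through REDCap secures the first. The second depends on the block sizes, on who knows the earlier assignments, and on whether those assignments are visible.

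Here the blocks are short, run separately within each site, and have their sizes in print. Every code goes to one role, which then places the participant in an arm, so that role knows the site's past assignments. This is an inference, but a direct one. The letter codes cannot hide the arm from the person who makes the assignment.

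The primary outcome is the self-reported BAI, and control patients wait until after the 12-month follow-up for the programme. If the order or timing of entry were influenced by a guess about the next arm, the arms could differ in motivation or readiness. The covariates given as examples under Clinical outcomes are disorders, depressive symptoms, medication and psychotherapy. Adjusting for these would remove at best part of such a difference.

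**Working it through.** **Inputs from the protocol article.** Block sizes 2, 4 and 6, stratification by site and 1:1 allocation (assignment and Trial design sections). Four regions (Study setting). 207 per arm (Sample size), so 414/4 = about 104 per site if sites are equal. The article gives no figure for predictability, so there is none to reproduce. Its sample size does reproduce: a 4-point difference with SD 12.5 gives 154 per group by the normal approximation against 155 stated, and 155/0.75 = 207. This point leaves it unaffected.

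**Assumptions.** The observer knows the site's past assignments and the set of block sizes, but not where blocks begin later in the sequence. The article does not state how often each size is drawn; equal weights are the base case and are varied below.

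**By hand, at the start of a site's list, equal weights.**
- After one patient in arm A: P(next is B) = (1 + 2/3 + 3/5)/3 = 0.756.
- After A, A: P(next is B) = (1/6 × 1 + 1/5 × 3/4)/(1/6 + 1/5) = 0.864.
- After A, A, A: only a block of 6 is possible, so P(next is B) = 1.

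**Whole list.** Simulated sequences of 104, with exact Bayesian updating of the position within the block after each assignment. Blocks 2/4/6, equal weights:
- guesses correct: 70%;
- predictable at 0.75 or more: 59%; at 0.80: 52%; at 0.82: 25%; at 0.85: 17%; at 0.90: 6%; certain: 4%.

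Many predictions sit just above 0.80, so the 52% is sensitive to the cut-off. It is also sensitive to the weights:

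| Weights for 2:4:6 | Predictable at 0.80 or more |
|---|---|
| 2:1:1 | 58% |
| equal participants per size | 57% |
| 1:1:1 | 52% |
| 1:2:1 | 50% |
| 1:1:2 | 29% |
| 1:2:3 | 29% |

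Overall correct guesses stay at 69 to 71% in every row. Knowledge of the sizes is not needed for this: guessing whichever arm is behind in the site's running count also gives 70% under equal weights.

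**Alternatives, equal weights.**

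| Blocks | Correct | At 0.80 or more | Certain |
|---|---|---|---|
| 2/4/6 | 70.2% | 52% | 4% |
| 4/6/8 | 67.9% | 24% | 2% |
| 8/10/12 | 64.9% | 12% | 1% |

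**Relative effect on bias.** Suppose the expected outcome of a patient whose arm is guessed is shifted by eta BAI points towards the guessed arm. With g the probability that the guess is right:
- Acting on every guess: bias = 2 × (2g − 1) × eta. This gives 2 × 0.404 = 0.81 eta (2/4/6), 2 × 0.358 = 0.72 eta (4/6/8) and 2 × 0.298 = 0.60 eta (8/10/12). The reduction with 8/10/12 is 1 − 0.596/0.808 = 26%; with 4/6/8 it is 11%.
- Acting only when g is 0.80 or more: bias = 2 × eta × mean of (2g − 1) over all assignments, counting only those with g at 0.80 or more. This gives 0.72 eta, 0.35 eta and 0.18 eta. The reduction with 8/10/12 is 1 − 0.18/0.72 = 75%; with 4/6/8 it is 51%.

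The document gives no value for eta, so only the ratios are informative.

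**The case against.** The strongest reply is that a statistician-generated list with randomly varied blocks, released centrally after eligibility is verified, is a recognised method and nothing in the section is misstated. That stands: REDCap does conceal the sequence, and the concealment statement can fairly be read in that sense.

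A reader might infer that the coordinator makes soft eligibility judgements while knowing the likely next arm. The documents do not support this. The clinical evaluator conducts the baseline interview, nothing says evaluators see earlier allocations, and readiness and interest are absent from the Eligibility criteria section; they appear only as interview content. Release after verification also does most of what a further lock on the eligibility decision would do. What remains is order and timing, and these are constrained by the two-week window to baseline and the 48 hours for questionnaires. Some reordering of pending patients at a site is still possible.

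A reader might also multiply 0.72 by an eta of 1 to 2 points and set the resulting 0.7 to 1.4 BAI points against the planned 4. That does not hold either: eta has no source in the document, and the model would need every predictable patient to be shifted.

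Finally, larger blocks leave guessing at 65%, and withholding the sizes does not stop a guess from the running count. Both are true. The gain is mainly in removing confident predictions.

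**Conclusion.** The predictability is real. About 70% of next assignments at a site can be guessed by someone who knows the earlier ones, and this hardly depends on the block-size weights tried. The share predictable at 0.80 or more is about 29% to 58% under those weights; a flat statement that half are predictable holds only with weights near equal and that exact cut-off. Full certainty is rare, at about 4% under equal weights.

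The conclusion rests on four strata of about 104 patients and on the inference that the coordinator knows the past assignments. It is a vulnerability of the design. Nothing in the document shows that entry would be steered, and no bias in BAI points can be derived. The point is a cheap improvement and does not undermine the planned analysis.

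**What to change.** In the assignment section, replace the block sizes 2, 4 and 6 with larger random blocks that omit size 2, for example 8, 10 and 12, generated by the study statistician in the same REDCap module. State in the protocol that the sizes vary, and keep the sizes from the coordinator and the evaluators until enrolment ends. If recruitment has begun, apply the change to the unused part of each site's list.

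Expected gain under equal weights: correct guesses fall from about 70% to about 65%, and predictions at 0.80 or more from about 52% to about 12%. Bias under the selection model above falls by 26% if every guess is acted on, and by 75% if only guesses at 0.80 or more are.

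The cost is a new list, one changed sentence and slightly looser balance. With blocks up to 12 the worst case is 6 patients per site, or 4 × 6 = 24 overall: 195 v 219, with efficiency 4 × 195 × 219/414² = 0.997. The present blocks have a worst case of 3 per site, 201 v 213, with efficiency 4 × 201 × 213/414² = 0.999. The sample size does not change.
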